**Methods:**

The impact evaluation uses a cluster randomized controlled trial design with 2 outcome assessments. The first uses cross-sectional surveys of mothers of children aged 0-23 months and pregnant women before and after the interventions. The second is a cohort study of pregnant women followed until their child is 18 months from a subset of clusters. We will also conduct a process evaluation guided by the program impact pathway to assess coverage, fidelity, and acceptance. The study will be conducted in the Malang and Sidoarjo districts of East Java, Indonesia. The unit of randomization is the subdistricts. As random allocation of interventions to only 6 subdistricts is feasible, we will use constrained randomization to ensure balance of baseline covariates. The first intervention will be health system strengthening, including the Baby-Friendly Hospital Initiative, and training on counseling for appropriate infant and young child feeding (IYCF). The second intervention will be nutrition behavior change that includes *Emo-Demos*; a national television (TV) advertising campaign; local screening TV spots; a free, text message service; and promotion of low-cost water filters and hygiene practices. The primary study outcome is child stunting (low length-for-age), and secondary outcomes include length-for-age Z scores, wasting (low weight-for-length), anemia, child morbidity, IYCF indicators, and maternal and child nutrient intakes. The sample size for each cross-sectional survey is 1400 mothers and their children aged <2 years and 200 pregnant women in each treatment group. The cohort evaluation requires a sample size of 340 mother-infant pairs in each treatment group. We will seek *Gatekeeper* consent and written informed consent from the participants. The intention-to-treat principle will guide our data analysis, and we will apply Consolidated Standards of Reporting Trials guidelines for clustered randomized trials in the analysis.

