### Sampling Design and Sample Size

#### Sample Size

We estimated the targeted sample size for the study using the following assumptions: (1) in the 51 subdistricts in the Malang and Sidoarjo districts, there is a total population of approximately 4.4 million, with an average of approximately 86,000 per subdistrict; (2) assuming a crude birth rate of 17 per 1000 population per annum, 5% refuse, and 10% data losses, each subdistrict cluster would yield an average of 620 live births over 6 months; (3) an expected prevalence of stunting for children aged 0-23 months of 35% in the control clusters (based on unpublished survey data from Brebes, West Java, and Indonesian DHS data); (4) 80% power and 5% 2-sided alpha, and 1:1 ratio of interventions (subdistricts with and without the Baduta program) allocated; (5) design effect of 1.5 (lower than reported for the 2011 Indonesia DHS survey because of larger sized clusters); and (6) expected percentage point difference in the prevalence of stunting (0-23 months) between the intervention groups of 6% (35.0% in the control to 28.9% in the intervention group). (This is a relative reduction of 17%, which is lower than the 29% reduction in stunting reported in a recent meta-analysis [47] of education interventions to improve complementary feeding.)

A standard formula using established methods [48] for comparison of proportions to calculate the number of subjects required per intervention arm to test H_0_: *π*_0_=*π*_1_ is as follows:

where *z_α_*_/2_ and *z_β_* are standard normal distribution values for upper tail probabilities of *α*/2 and *β,* respectively, *π*_0_ is the proportion in control, *π*_1_ is the expected proportion in intervention, *m* is the number of individuals per cluster, and *ρ* is the intracluster correlation coefficient.

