Based on this calculation, the sample size required is 1392 mother-infant dyads from each group of 6 subdistrict clusters or approximately 232 mother-infant dyads per subdistrict cluster. We will round this up to 2800 mother-infant dyads per cross-sectional survey or 234 per subdistrict cluster. This sample size will provide 80% power assuming a Z score SD of 0.975 and 5% level of significance to detect a 0.15 Z score difference in height-for-age Z scores [49] between the intervention and the control groups in the end-line survey. Therefore, for the cross-sectional evaluation, we will select 2800 mothers of children aged 0-23 months and an additional 400 pregnant women from 12 subdistricts within the Sidoarjo and Malang districts.

For the cohort evaluation, to detect a difference in mean length-for-age Z score between the experimental and control groups at an end line of 0.35 Z score [50], assuming 80% power and 5% level of significance, with a design effect of 1.5 (see above), we will require a sample size of 272 mother-infant pairs in each of the intervention and comparison groups. Assuming a dropout rate of 25%, we need to recruit 680 mother-infant pairs (56-57 per subdistrict cluster).

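### The cohort target of 680 multiplies by 1.25 where 25% dropout needs division by 0.75 (726); separately, the 80% power for 0.15 Z and the cohort's 272 per arm do not follow from the inputs stated

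*Protocol article*

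**What the plan says.** All the figures are in the protocol article, mainly under Sample Size.

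- **Common assumptions.** The list opens with "80% power and 5% 2-sided alpha, and 1:1 ratio of interventions" and includes a "design effect of 1.5 (lower than reported for the 2011 Indonesia DHS survey because of larger sized clusters").
- **Survey.** The size comes from stunting prevalence: "We will round this up to 2800 mother-infant dyads per cross-sectional survey or 234 per subdistrict cluster". The article then adds that the survey "will provide 80% power assuming a Z score SD of 0.975 and 5% level of significance to detect a 0.15 Z score difference"; the outcome there is height-for-age at end line. This is the only SD given in the section.
- **Cohort.** For a difference of 0.35 Z at 80% power, 5% significance and the same design effect of 1.5, the article requires 272 pairs per arm. It gives no SD here. It continues: "Assuming a dropout rate of 25%, we need to recruit 680 mother-infant pairs (56-57 per subdistrict cluster").
- **Abstract, Methods.** The inflated figure is repeated: "The cohort evaluation requires a sample size of 340 mother-infant pairs in each treatment group".
- **Results, Cohort Evaluation.** Of 685 mothers followed, 331 control and 327 intervention participants stayed to the end, with 12 and 15 dropouts.

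**The concern.** If 272 per arm is the number needed at the end of follow-up, recruitment has to be large enough that 272 remain after the assumed loss. Adding 25% to 272 does not do that, because the loss applies to the larger recruited number. The published target would then miss the plan's own requirement under the plan's own dropout rate.

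The two power statements for length-for-age raise a different problem: a reader cannot rebuild either from the inputs given. Mean length-for-age Z is the cohort's primary outcome, so the basis of its sample size matters. These figures are also likely to be carried into trial reports and reused when similar evaluations are planned.

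**Working it through.** **Inputs from the article:** two-sided 5%, 80% power, 1:1 allocation, design effect (DE) 1.5; survey 1400 per arm, SD 0.975, difference 0.15 Z; cohort 272 per arm, difference 0.35 Z, dropout 25%. Normal quantiles: 1.960 + 0.842 = 2.802, squared 7.849.

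**1. Dropout**

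- The plan's figure reproduces as 272 × 1.25 = 340 per arm; 2 × 340 = 680; 680/12 = 56.7 per subdistrict.
- Correct inflation: 272/(1 − 0.25) = 362.7, so 363 per arm and 726 in total; 726/12 = 60.5 per subdistrict. The shortfall is 726 − 680 = 46 pairs, or 46/726 = 6.3%.
- What 340 leaves at 25% loss: 340 × 0.75 = 255 per arm.
- Loss that 340 can absorb: 1 − 272/340 = 20%.

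**2. Survey, 0.15 Z**

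- Standard error = 0.975 × √(2 × 1.5/1400) = 0.0451.
- Power = Φ(0.15/0.0451 − 1.960) = 91.4%.
- Difference detectable at 80% power = 2.802 × 0.0451 = 0.126 Z.
- Variants at SD 0.975: no design effect, 98.3%; one-sided with DE 1.5, 95.3%; t test with 10 df and DE 1.5, 84.9%. A difference-in-differences comparison gives 65.2% with DE 1.5 and 82.1% with none, but the sentence is about the end-line survey and a DE is stated.
- What 80% would need: SD = 0.15/(2.802 × √(3/1400)) = 1.16 at DE 1.5, or DE = 0.15² × 1400/(2 × 7.849 × 0.975²) = 2.1 at SD 0.975. The article states neither.

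**3. Cohort, 0.35 Z**

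- With the one stated SD: 2 × 0.975² × 7.849/0.35² = 121.8, so 122; 122 × 1.5 = 183 per arm, not 272.
- SD implied by 272: 0.35/(2.802 × √(2 × 1.5/272)) = 1.19.
- Power with 255 per arm at that SD: Φ(0.35/(1.19 × √(3/255)) − 1.960) = 77.4%.

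**4. What happened**

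- Dropouts: 12 + 15 = 27 of 685 = 3.9%. Completers: 331 + 327 = 658, against 2 × 272 = 544, a surplus of 114. Each arm is above 272.

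**The case against.** The strongest reply is that nothing was lost. Dropout was 3.9%, both arms finished above 272, and even at 25% loss the cost would have been under three points of power. That stands, and it makes this a correction to reporting rather than a threat to the trial.

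The reply on the survey is also largely sound. At the stated SD and design effect, 0.15 Z has more power than claimed. Length-for-age Z is a secondary outcome in the cross-sectional evaluation, and the 2800 was set by stunting prevalence, so this sentence decided nothing.

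A reader might infer that the section contradicts itself by using two SDs for one outcome, and that this is why the 80% fails. The document does not support that:

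- It states one SD. The 1.19 is solved backwards from 272, so it is an inference about an input left unstated.
- The 0.15 Z figure fails on its own stated inputs, whatever SD the cohort used.
- The SDs need not be equal. The survey covers children aged 0–23 months. The cohort follows children to 18 months and excludes, among others, twins and infants with visible congenital defects.

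Finally, the 77% depends on 272 being the right requirement. If the cohort SD were 0.975, 183 per arm would do and 255 completers would give 91% power; at 1.16 they would give 79.4%. This limits the power figure. It does not rescue the step from 272 to 340, which is wrong for 25% loss under any SD.

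**Conclusion.** The point holds in three separate parts.

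- **Dropout.** 680 is wrong for 25% loss. Given 272 per arm, the target is 726, a shortfall of 46 pairs; 680 fits 20% loss. The power cost at 25% loss is about 2.6 points (80% to 77.4%), on the assumption that 272 gives 80%.
- **Survey power.** The 80% for 0.15 Z does not follow from SD 0.975, 1400 per arm and DE 1.5, which give about 91% (0.126 Z detectable at 80%). The error is on the safe side at the stated inputs.
- **Cohort SD.** 272 does not follow from the only SD in the section. It needs about 1.19 at DE 1.5, which the article does not state.

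It would go too far to say that the cohort was underpowered in the event: 658 pairs completed against 544 required. These are minor errors in planning figures, and they remain in the published justification.

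**What to change.** Change the text only:

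1. Give the cohort target as 726 (363 per arm, 60–61 per subdistrict) at 25% loss, or keep 680 and say that it preserves the required 272 per arm for losses up to 20%. Make the Abstract agree.
2. State the SD behind 272 per arm and its source. It need not equal the survey's SD. If the SD turns out not to support 272, recompute that figure before inflating it.
3. Correct the survey sentence to 0.126 Z at 80% power, or about 91% power for 0.15 Z, at SD 0.975 and DE 1.5. Otherwise give the SD (about 1.16) or the design effect (about 2.1) that produces 80%.

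The cost is a few sentences. No further enrolment is needed, since completers already exceed the requirement.

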#### Recruitment and Consent

We have described the approach and criteria for selecting clusters in the section above on *Cluster Selection and Design of Randomization*. We will seek *Gatekeeper* consent [26] from the heads of the 2 study districts, the selected subdistricts, and the sampled villages.

In both the cross-sectional and cohort evaluations, we will recruit either women with children aged <2 years or pregnant women from the village-level sampling frames by contacting them at home. Trained field staff will explain in detail the background and objectives of the study to the women and provide a written information sheet to all women contacted. Written informed consent was obtained from women who agreed to participate in the study.

### Data Collection Methods

#### Data Collection Team

An organization not responsible for the intervention will recruit and manage a data collection team. For the cross-sectional evaluation, we will recruit 10 field coordinators, 130 interviewers, and 20 nurses or midwives to collect blood samples and to take anthropometric measurements. We will divide the staff into 10 field teams, with each team consisting of 1 field coordinator, 1 assistant field coordinator, 8 enumerators for interviews of mothers and caregivers of children aged <2 years, 2 interviewers for pregnant women, 1 interviewer for dietary data, and 2 anthropometry field workers who also collected the finger-prick blood sample for hemoglobin assessment using Hemocue. We will train the cross-sectional evaluation team for 1 week on an overview of the Baduta study, the use of the CommCare data capture app, household listing and data collection procedures, explanations of study instruments (listing forms and questionnaires), quality controls for data collection, and a field plan. The training will include a 1-day tryout to practice the household listing, interviews of mothers of children, and pregnant women using the CommCare data capture app.

For the cohort evaluation, we will recruit 2 field coordinators and 8 interviewers, all of whom will be graduates from a local nutrition academy. We will divide this staff into 2 field teams, 1 team for each district. We will train the cohort evaluation team for 1 week on an overview of the Baduta study, use of the CommCare data capture app, the schedule of cohort data collection, explanations of study instruments, anthropometry, dietary and hemoglobin assessment, and tryout of all the cohort data collection procedures. The 2-day training for blood collection will cover standard phlebotomy methods, use of Hemocue for hemoglobin assessment and its calibration, and a practice session in the field. The 2-day training for anthropometric measurements will be competency based and will use standardization procedures to check the performance (precision and accuracy) of the anthropometry field workers.

#### Data Collection Schedule

For the cross-sectional evaluation, we will conduct a household listing in each subcluster (hamlet) before the interviews to obtain a list of all children aged <2 years and pregnant women living in the subcluster. We will identify households by applying a sticker that has an identification number for each house listed. We will interview women at home but invite and accompany them and their selected children (aged <2 years) to a central location in the village to collect blood samples and record anthropometric measurements. We will use the same field methods for both the baseline and end-line surveys. We will conduct the end-line survey 2 years after the baseline survey.

For the cohort evaluation, the data collectors will visit each woman a total of 15 times from late in the third trimester of pregnancy until the child is 18 months old (Figure 3).

#### Types of Information Collected

For the cross-sectional evaluation, we will use the *house-listing form* (paper based) to record the identification number and collect household location and composition, including details about each member such as date of birth and gender. We will use a *registration module* (part of the CommCare app) to record the name and address of the potential respondents selected based on the house-listing form. This module will then direct interviewers to the appropriate questionnaire modules for children aged <2 years or pregnant women. The respondent will be either the mother and caregiver of the child aged <2 years or the pregnant women. The *questionnaires for children aged <2 years* (CommCare) will record the family sociodemographic characteristics, the history of pregnancy and delivery, the history of antenatal care services, exposure to the interventions (end line only), breastfeeding practices, use of integrated village health posts, morbidity, knowledge about breastfeeding, self-efficacy for breastfeeding, socioeconomic status, food security, and use of mobile phones.

Similarly, the *questionnaires for pregnant women* (CommCare) will record family sociodemographic characteristics, the history of pregnancy and delivery, exposure to interventions, knowledge about breastfeeding, knowledge about food to eat during pregnancy, intention to breastfeeding, socioeconomic status, and food security. We will use a special-purpose module (CommCare) to record the *anthropometric and hemoglobin measurements*. We will capture *dietary intake data* from children aged <2 years and pregnant women using the multiple-pass 24-HR (paper-based).

For the cohort evaluation, in pregnancy and until the child is 18 months old, the field staff will collect information about the location and composition of the household, pregnancy knowledge, breastfeeding intention, infant feeding knowledge, household food security, birth outcome and delivery services, antenatal care, IYCF practices, utilization of integrated village health post services and immunizations, exposure to Baduta interventions, child morbidity, maternal and child dietary intake, maternal and child anthropometry, and hemoglobin assessment (Figure 3). We will capture *dietary intake data* from the children and pregnant women using the multiple-pass 24-HR (paper based for the women and electronic data capture for the children).

#### Digital Data Collection Tool

We will capture data electronically on Android tablets in the field using a special-purpose CommCare app developed for the study. The interviewers will record the information on structured, error-detecting forms on tablets or mobile devices and dispatch it directly to a server for cleaning and merging. The app will navigate the interviewers through the different questionnaires for women with a child aged <2 years or pregnant women or the different visit forms in the cohort evaluation. We will generate and distribute routine field team performance reports based on the data captured to help supervisors manage field activities.

### Statistical Methods

The intention-to-treat principle will guide our data analysis, and we will include data from all participants even if they do not participate in all interventions. We will apply the guidelines of the Consolidated Standards of Reporting Trials statement for clustered randomized trials in the analysis and presentation of the results. We will conduct analyses at the woman or infant level adjusted for cluster randomization. Initially, we will assess the effectiveness of randomization by comparing potential confounding factors in both treatment groups. We will apply statistical tests with χ^2^ tests for categorical variables and an adjusted Wald test or the Fisher exact test for continuous variables to assess for any significant difference between treatment groups. *P* values <.05 will be considered to indicate a statistically significant difference between the groups. For selected dietary analyses of continuous variables, we will use the nonparametric rank order statistic, Somers’ D [51] (corresponding to rank-sum tests), as it can adjust for the cluster sampling design.

We will calculate frequency and percent distributions for categorical variables and mean and SD or median and interquartile range for continuous variables. We will characterize the dietary intake by age group, breastfeeding status (for infants aged 12-23 months), and intervention and comparison groups. We will generate medians and interquartile ranges for dietary intake distributions that are not normally distributed. We will plot the frequency distribution of IYCF practices by child age. We will also plot the frequency distribution of Z score indices (Z score curves) in 0.25 Z score intervals using a Lowes function to smooth the curves, and we will compare these distributions with the growth standard distribution. We will repeat these plots broken down by treatment groups.

For the cross-sectional evaluation, the primary analyses will compare the prevalence of stunting (low length-for-age<–2 Z score) and the 95% confidence intervals in each treatment group adjusted for clustering and any imbalanced baseline characteristics.

For the cohort evaluation, the models will include the treatment group as a fixed effect, the community cluster as a random effect to account for the cluster effect, and the impact of the interventions over time by testing for an interaction between time and intervention group. We will conduct analyses to identify the subgroups (eg, level of maternal education or household wealth categories) that modify the response to the intervention. We will check the model assumptions and make appropriate adjustments to the analysis where necessary. Secondary analyses will examine each outcome variable (length-for-age Z scores, feeding patterns, and mean nutrient intakes), taking into account the repeated measurements within children by using separate mixed models.

Linear mixed models will be used for continuous outcomes (eg, length-for-age Z scores), and generalized linear mixed models will be used for noncontinuous outcomes (eg, mixed logistic models for binary outcomes, such as, percentage exclusively breastfeeding). Models will include intervention or comparison groups as a fixed effect, infants as a random effect to account for repeated measurements, and community cluster as a random effect to account for cluster effects. We will use Stata V.15 (Stata Corp 2017; Stata Statistical Software: Release 15; Stata Corp LP) for all analyses.

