### Cluster Selection and Design of Randomization

The unit of randomization for the study will be subdistricts, selected by the authors to prevent contamination as they will deliver the health system strengthening interventions through the subdistrict community health centers. It will only be feasible to randomize a limited number of subdistricts to the new interventions versus the standard programs. As we will be limited to 12 subdistrict clusters (6 intervention and 6 usual programs), it will not be possible to use simple randomization to allocate them randomly to the intervention or control groups.

We will use constrained randomization [30,31] to ensure a balanced distribution of covariates in the study treatment groups because of the limited number of subdistrict clusters in which it is feasible to conduct the study. There are 33 subdistricts in Malang and 18 subdistricts in Sidoarjo. We will exclude subdistricts with similar ongoing projects and small subdistricts (population <70,000), leaving 24 subdistricts eligible for the study.

We will conduct hierarchical cluster analysis on the 24 eligible subdistricts using data for each district from the 2011 Village Potential Statistics (Pendataan Potensi Desa/Kelurahan) data set and local health surveillance data. We will use indicators of household economic status, access to health care, and prevalence of undernutrition in children to identify a group of similar subdistricts. We will select a group of 12 of the most similar subdistricts and construct a list of the 924 possible combinations of 6 intervention subdistricts and 6 comparison subdistricts. We will perform the analyses for constrained randomization with SAS 9.2 (SAS Institute Inc) using an algorithm developed by Chaudhary and Moulton [32].

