We will select combinations of intervention and comparison subdistricts with balanced covariates, as measured by a difference in (1) the average distance of the neighborhood to the closest community health care center with a cutoff value for balance <0.5 km, (2) the coverage of children weighted at village health posts with a cutoff value for balance <5%, (3) the prevalence of underweight children (weight-for-age less than –2 Z score from growth monitoring charts) with a cut off value for balance <2.5%, (4) the ratio of village health posts to the total population with a cutoff value for balance <1.6/10,000 population, and (5) the percentage of low-income families who have a local government Certificate of Disadvantage (Surat Miskin/Surat Keterangan Tidak Mampu) with a cutoff value for balance <5%. Using simple random sampling, we will select one of the balanced combinations of subdistricts for allocation of the study interventions.

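### The primary cross-sectional analysis takes its covariates from observed baseline imbalance instead of a set fixed in advance, and the Fisher exact test is assigned to continuous variables

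*Protocol article*

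**What the plan says.** All of the analysis text at issue is in the Statistical Methods section of the protocol article. It begins with a check on the allocation: "Initially, we will assess the effectiveness of randomization by comparing potential confounding factors in both treatment groups". The tools for that check are chi-square "tests for categorical variables and an adjusted Wald test or the Fisher exact test for continuous variables", and *P* "values <.05 will be considered to indicate a statistically significant difference between the groups". For the cross-sectional evaluation, the primary comparison of stunting prevalence is then to be "adjusted for clustering and any imbalanced baseline characteristics". No covariate is listed.

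The same section makes a general statement about clustering: "We will conduct analyses at the woman or infant level adjusted for cluster randomization".

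Under Cluster Selection and Design of Randomization, the trial is "limited to 12 subdistrict clusters (6 intervention and 6 usual programs"). Allocation is constrained on five subdistrict variables with absolute cutoffs: "We will select combinations of intervention and comparison subdistricts with balanced covariates". Statistical Methods names neither these five variables nor the two districts as model terms.

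**The concern.** Subdistricts are randomized and the baseline survey comes before the interventions. Differences between arms at baseline therefore arise by chance, within the limits set by the constrained allocation. A significance test on such differences does not show which variables are worth adjusting for. That depends on how strongly a variable predicts stunting, and this can be judged beforehand.

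The protocol already has that knowledge. Its Background links low maternal height to growth faltering, and lower maternal education and household wealth to stunting. Study Setting gives under-five stunting of 24% in Sidoarjo and 31% in Malang. Under the stated rule each of these enters the primary model only if it looks imbalanced.

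Two things are at stake: whether the primary model is free of choices driven by chance, and the precision that strong predictors would give. Separately, the Fisher exact test cannot be carried out on a continuous variable as the text describes.

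**Working it through.** **Inputs from the protocol.** Stunting 35.0% v 28.9%, two-sided alpha 5%, power 80%, design effect 1.5, 1392 dyads per arm, about 232 per subdistrict (Sample Size); 12 clusters (Cluster Selection); 2435 mother-child pairs in the baseline survey (Results).

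**Assumptions.** The number of baseline covariates tested (5, 10 or 20), their independence, and any intracluster correlation above the one implied by the design effect.

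**1. The plan's own sample size.** With the standard two-proportion formula (pooled variance under the null):

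n = [1.96·√(2·0.3195·0.6805) + 0.842·√(0.35·0.65 + 0.289·0.711)]² / 0.061² ≈ 916.05, rounded up to 917.

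917 × 1.5 = 1375.5, against 1392 stated (1.2% apart). The design effect is thus the one used in the plan, and nothing below changes this number.

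**2. Chance flags when every test has a true 5% size.** P(at least one) = 1 − 0.95^k.

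| k | P(at least one flag) |
|---|---|
| 5 | 23% |
| 10 | 40% |
| 20 | 64% |

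This step does not depend on how clustering is handled.

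**3. Conditional case: a baseline test that ignored clustering.** True size = 2·[1 − Φ(1.96/√DE)].

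- At DE = 1.5: 1.96/1.2247 = 1.600, giving 0.110.
- The implied correlation is 0.5/(232 − 1) = 0.0022. At the achieved baseline size of 2435/12 ≈ 203 per cluster, DE = 1 + 202 × 0.00216 = 1.44, giving 10.2%. A simulation of 12 clusters of 203 (20,000 runs) gave 10.1%.
- At assumed correlations of 0.01, 0.02 and 0.05 the formula gives about 26%, 38% and 56%, and the simulation 26%, 38% and 55%.
- In the same simulations a cluster-level t test on 10 df stayed between 4.9% and 5.1%.

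**4. District as an example of a known predictor.** The gap between districts is 31 − 24 = 7 points; the effect sought is 35.0 − 28.9 = 6.1 points. District is not among the five balancing variables. If one arm had one more Malang subdistrict than the other, the expected arm difference in stunting level would move by 7/6 ≈ 1.2 points. The district figures are for under-fives, and the article does not report the district split, so this is only an illustration.

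**5. Degrees of freedom.** 12 clusters − 2 arms = 10. Two cluster-level covariates leave 8.

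**The case against.** **Clustering.** A reader might infer that the baseline tests ignore clustering. The text does not support that. It says individual-level analyses are adjusted for cluster randomization, it calls the Wald test adjusted, and a chi-square test can be design-corrected. What stands is narrower: adjustment is unstated for the chi-square test, and the Fisher exact test has no usual cluster-adjusted form. The 11% figure is therefore conditional. It also borrows a design effect that was set for stunting, not for baseline factors.

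**P<.05 as the definition of imbalance.** The section never says this outright. The threshold can be read as the general alpha, and where the protocol does define balance, for the allocation, it uses absolute cutoffs. The link is a strong inference, because Statistical Methods offers no other criterion. Under any criterion applied to observed differences, the covariate set would still depend on the data.

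**A separate analysis plan.** A covariate list is commonly left to such a plan, and its absence here is not the point. The article states a rule, and a fixed list elsewhere would contradict it.

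**Balance is worth looking at.** With 12 clusters, and a fresh end-line sample recruited after the programme has run, arms could differ through selection as well as chance. This is a good reason to display balance, but not to test it and build the model from the result.

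**Size of the harm.** The percentages count flags on covariates. They do not measure bias or error in the treatment comparison, and a chance flag on a variable unrelated to stunting does little. Correlated covariates, such as education and wealth, would also make at least one flag less likely than under independence.

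**Conclusion.** The point holds for the primary cross-sectional analysis. The covariate rule is open-ended and data-dependent, although the useful predictors are known and the survey collects the data for them. The cohort models carry no such rule and are not affected.

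With correctly sized tests, the chance of at least one spurious flag is 40% for 10 covariates and 64% for 20; the counts and independence are assumptions. The rate of about 11% per test applies only if the chi-square test is unadjusted, and should not be read as the plan's expected error rate. Nor do these figures show that the type I error of the stunting comparison is inflated, because that was not calculated.

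Naming the Fisher exact test for continuous variables is a plain error. It is confined to the baseline comparison and touches no outcome analysis. Both matters should be corrected; neither affects the sample size.

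**What to change.** In Statistical Methods:

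- Describe baseline balance by arm with summaries only, and remove the significance tests, including the Fisher exact test for continuous variables.
- Replace the clause on imbalanced characteristics with a covariate set fixed before the end-line analysis. A reasonable set is district and subdistrict baseline stunting prevalence at cluster level, and child age, child sex, maternal height, maternal education and household wealth at individual level.
- Leave out the separate baseline-prevalence term if the model already compares change from baseline, as the Cross-Sectional Survey Assessment section describes.

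Other sensible lists exist. What matters is that the list is fixed without reference to observed imbalance.

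The cost is mainly wording. Dates of birth, sex, maternal height and socioeconomic status are already recorded; maternal education is presumably among the sociodemographic items and should be confirmed. Up to two cluster-level degrees of freedom are spent, leaving 8 of 10. The requirement of 1392 per arm is unchanged.
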